### Storing vitamin D and placebo suppositories

The basis of the suppository is mono, di, and triglyceride called AM-15 suppository and synthesized by *Gattefosse France*. The base melting point is 34–36 degrees. Suppositories will be produced by melting and molding under the supervision of a pharmacist and will be produced by pharmaceutical experts from the pharmaceutical laboratory of the Faculty of Pharmacy of Mashhad University of Medical Sciences, Mashhad, Iran. Each suppository drug weighs 1 gram and contains 1000 units of vitamin D3. They have a sufficient mechanical strength and a smooth, uniform, whitewashed surface. After producing the suppositories, the correct amount will put in in tight plastic packages and placed in plastic containers at a temperature below 25 degrees, preferably kept in the refrigerator. Placebo suppositories will be made in exactly in the same way using Suppocire AM-15, with the exception that they lack the medication. They will be similar to pharmaceutical suppositories in terms of shape and color.

### Intervention program and patient education

During the first visit, the vaginal suppositories (without identifying the type of suppository, only having an identifier code inside the appropriate envelopes) will be given to the participant. The method and duration of use, as well as the follow-up time will be taught by the researcher to each participant. A phone number will be provided to ensure that the supplements are properly used and participants will reminded to keep track of the follow-up time. The researcher’s phone number will be shared with the participants to contact them if they have any questions about how to use the suppositories and/or if they experience any problems or signs of burning and itching following the use of the suppositories. As noted above, the total time period to take the suppositories for each postmenopausal woman will be 8 weeks, during which the investigator will monitor the use of the suppositories in the women by telephone or text-messaging (based on the convenience of the participant).

### Teaching the participants on how to use vaginal suppositories

Participants will be informed that (i) the suppository should be placed inside vagina before bedtime, but should not be inserted more than 3 inches inside the vagina, (ii) before placing the suppository in the vagina, their hands should be washed with water and soap, (iii) every night, only one suppository should be inserted into vagina, and (iv) the treatment schedule will be every night for 2 weeks and every other night for 6 weeks.

### Primary outcome measurements

Sexual function will be the primary outcome measure,. This will be assessed using the Female Sexual Function Index (FSFI). The FSFI comprises 19 questions of sexual function in six independent areas consisting of desire (two questions), arousal (four questions), lubrication (four questions), orgasm (three questions), sexual satisfaction (three questions) and pain from sex (three questions). Responses to the desire items are made on a six-point Likert scale from 0 (*never*) to 5 (*completely*) with a minimum score of 1 and a maximum score of 6. For other areas, responses are also made on a six-point Likert scale from 0 (*none*) to 5 (*completely*) with a minimum score of 0 and a maximum score of 6 [33]. The validity of the Persian version of this scale was evaluated and validated by Mohammadi et al. [34].

### Secondary outcomes

The secondary outcome measure will be participants’ satisfaction with the intervention.

### Baseline assessments

Evaluation of sexual function in postmenopausal women will be performed among all three groups at the beginning of the study and before the intervention.

### Follow-up assessments

Sexual function of women among all three groups immediately after the end of the intervention (duration of the intervention will be 8 weeks), and one and 2 months after the end of the intervention.

### Safety issues

Overall, the total intake dose of vitamin D3 will be 32,000 units during the 8 weeks of the intervention. The risk of poisoning with vitamin D is due to an overdose of vitamin D3 is 50,000 units per month (according to the Iran’s national guidelines) if administered over a long period of time. Given that the overall dose used in the proposed study is much lower than the level considered by the country’s guidelines, the probability of poisoning is low. In addition, to address concerns about the likelihood of poisoning with vitamin D3, the participants would be asked to withdraw taking supplemental vitamin D3 during the study. In addition, all symptoms of vitamin D3 poisoning will be taught to them and they will be asked to discontinue the supplements and inform the researcher if the signs of intoxication are detected. Any side-effects will be reported at the end of study.

### Data management and analysis

Data analysis and management will be performed using the SPSS software version 25. After collecting data, data entry will be performed on the dataset designed by ZS. The data entry accuracy and screening will be performed under the supervision of the ZA and MM. Initially, the normal distribution of data is investigated using the Kolmogorov-Smirnov test. In the case of normal distribution of data, the comparison of the mean scores of sexual function between the groups will be carried out using the repeated measurements ANOVA test. If the test is significant, a post-hoc test is used to determine the difference between the groups. Comparison of demographic and fertility characteristics of the women in the groups will be performed using appropriate statistical tests such as chi-square tests and one-way ANOVAs. If the assumption of normality is violated, transformation of data will be used. In most cases, transformation will result in normally distributed data and then parametric tests will be the main statistics employed. If not, a mixed effect model or non-parametric statistics will be used. A significance level of *p* < .05 will be used for statistical analysis.

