### Sample size estimation

According to previous study by Çayan et al. [32], considering α = 0.05, power = 80%, moderate effect size 0f 0.6, the sample size for the research study was estimated to be 25 people for each group. Considering the attritional loss of 40% of the samples in the research process, the sample size for each group was calculated to be 35 people. The sample size calculation was performed according to primary outcome of study.

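### A normality pre-test picks the primary method and scale, the last fallback is left open, and the default repeated-measures ANOVA is not set up to use baseline FSFI or partial follow-up

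*Protocol article*

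**What the plan says.** The section Data management and analysis sets out a sequence.

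- First step: "Initially, the normal distribution of data is investigated using the Kolmogorov-Smirnov test".
- If the data are normal: "the comparison of the mean scores of sexual function between the groups will be carried out using the repeated measurements ANOVA test", with a post-hoc test between groups if the result is significant.
- If they are not normal, the data are transformed.
- If transformation does not work: "If not, a mixed effect model or non-parametric statistics will be used".

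The section does not say which visits enter the ANOVA, whether the group effect or the group-by-time term decides, or how missing visits are handled. It mentions no adjustment for baseline FSFI.

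Three other places bear on this.

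- The Methods part of the Abstract lists four FSFI assessments: baseline, end of treatment, and one and two months later.
- Goals and hypotheses includes baseline in the within-group objective, but limits the between-group objective to the three post-treatment assessments.
- Sample size estimation plans for heavy loss: "Considering the attritional loss of 40% of the samples in the research process".

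**The concern.** Two faults are in the text itself.

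1. **The outcome data choose the method.** The test is applied to the data, which as written means the scores and not the model residuals. Its result can change both the method and the scale on which the treatment effect is expressed. The last step offers two different analyses with no rule for choosing between them.
2. **The mixed model has the wrong trigger.** A standard linear mixed model also assumes normal residuals, so it does not remedy non-normality. Its advantage here is that it can use women with some but not all follow-up scores. On the default path that advantage is unavailable, in a trial that expects 40% loss.

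Two further weaknesses follow from the default method. It does not use the baseline score as a covariate, which costs precision. In its classical form it needs every score in the model, so one missed visit removes a woman entirely.

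A third weakness is conditional. If baseline is a level of the time factor and the group main effect decides, the comparison averages in a visit at which randomisation makes the expected difference zero.

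**Working it through.** **The plan's own figure.** Sample size estimation gives "considering α = 0.05, power = 80%, moderate effect size 0f 0.6" and 25 per group before attrition. If 0.6 is read as a standardised mean difference, a two-sided two-sample t-test at a single visit needs 45 per group, and 25 give 55% power. A three-group repeated-measures ANOVA group effect with f = 0.3 and correlation 0.5 needs 24 (four visits) or 25 (three visits), but the article states neither f nor a correlation. The 25 is therefore taken as given. Whether it is right is a separate matter.

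**Inputs.** From the article: effect 0.6, alpha 0.05, 25 per group, 35 enrolled per group, 40% attrition, four assessments. Assumed: 0.6 is a difference in SD units and is constant over the three post-treatment visits, the test is two-sided, SD is 1 at every visit, and the correlation rho between any two visits is equal (0.3, 0.5 or 0.7).

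**Effect and variance under four readings, vitamin D against placebo**

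- Four-visit group effect: effect (0 + 0.6 + 0.6 + 0.6)/4 = 0.45, variance (1 + 3rho)/4.
- Unadjusted mean of the three post-treatment visits: effect 0.6, variance (1 + 2rho)/3.
- Post-treatment mean minus baseline (a single group-by-time contrast): effect 0.6, variance (1 + 2rho)/3 + 1 − 2rho.
- Baseline-adjusted post-treatment mean: effect 0.6, variance (1 + 2rho)/3 − rho².

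The standardised effect is effect/√variance. At rho = 0.5:

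- 0.45/√0.625 = 0.57
- 0.6/√0.667 = 0.73
- 0.6/√0.667 = 0.73
- 0.6/√0.417 = 0.93

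Power comes from the noncentral t distribution with 2n − 2 degrees of freedom and noncentrality equal to the standardised effect × √(n/2).

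| Analysis, 25 per group | rho 0.3 | rho 0.5 | rho 0.7 |
|---|---|---|---|
| Four-visit group effect | 62% | 50% | 43% |
| Post-treatment mean, unadjusted | 81% | 72% | 64% |
| Post minus baseline | 58% | 72% | 91% |
| Post-treatment mean, baseline-adjusted | 88% | 90% | 96% |

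**Overall three-arm test.** This was checked by simulation: 4,000 replicates, one arm raised by 0.6 at all post-treatment visits, 25 per group, rho 0.3/0.5/0.7.

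- Group main effect over four visits: 66.1/52.1/44.8%.
- Group-by-time interaction: 42.5/57.9/82.9%.
- Baseline-adjusted post-treatment mean: 91.0/92.6/97.6%.

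The ranking agrees with the pairwise table: adjustment comes first throughout.

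**Attrition.** 35 × (1 − 0.4) = 21 per group, or 63 of 105 women. That is below the 25 per group that the plan requires. A classical repeated-measures ANOVA would be left with those 21 if every lost woman missed at least one visit and nothing was imputed.

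**The case against.** The strongest reply is that much of what could be charged here is not written in the article.

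- **Baseline as an outcome visit.** A reader might infer this from the four assessments and the within-group objective. The analysis section does not say it, and the between-group objective names only post-treatment visits. If the ANOVA follows that objective, the dilution to three quarters disappears. At rho = 0.5 the shortfall against the adjusted analysis is then 90 − 72 = 18 percentage points, not 90 − 50 = 40.
- **The group main effect as the deciding term.** The wording about comparing means between groups makes this a fair reading, but not the only one. The interaction is not diluted in this way.
- **A complete-case analysis that discards 40% of the women.** Listwise deletion is how the classical ANOVA works, but the article does not state it. Rules for missing data may stand in a fuller protocol or SAP that is not shown. The 40% is a sample-size allowance, not an exclusion rule. A mixed model would also recover only women with at least one post-baseline score.
- **Bias from dropout.** A simulation can be built in which complete cases understate the week-8 effect (0.53 against a true 0.60). That result depends on the dropout mechanism assumed for it and is not a property of this plan.
- **Validity.** In a randomised trial an unadjusted comparison is valid. Leaving baseline out costs efficiency and does not cause bias.

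All of these stand as limits on the claim. None touches what the article does state: the pre-test, the possible change of scale, the open last step, and a mixed model tied to non-normality. These are written rules, so the possibility of a separate SAP does not excuse them.

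**Conclusion.** The point holds in a limited form. The plan lets a normality test on outcome data choose the primary method and possibly the scale, ends in an open choice, and keeps the mixed model for a problem that it does not solve. The role of baseline and the deciding term are not fixed.

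A pre-specified, baseline-adjusted analysis has more power under every reading of the default. At 25 per group the gain over the better of the two unadjusted readings that avoid dilution is 7, 18 and 5 percentage points at rho 0.3, 0.5 and 0.7. Over the four-visit group effect it is 26, 40 and 53 points, but only if baseline is a level of the time factor and the group main effect decides.

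All these figures rest on a constant 0.6 SD effect, equal correlations and no missing scores among the women analysed. The effect of the pre-test on type I error or power was not quantified. The objection to it is that the primary analysis is not fixed in advance.

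**What to change.** Replace the sequence with one primary analysis, used whatever the Kolmogorov-Smirnov result:

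- A linear mixed model (MIXED in SPSS 25) of the three post-treatment FSFI scores, with fixed effects for arm, visit, arm-by-visit and baseline FSFI, and an unstructured covariance matrix.
- Every randomised woman with at least one post-baseline score, analysed in her assigned arm.
- A named deciding contrast: which arms, and whether averaged over the three visits or at one stated visit. The power figures above are for the average over visits. A single visit would give less.
- No transform-or-switch rule. Check the model residuals and report bootstrap intervals as a sensitivity analysis.

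This matches the between-group objective and uses partial follow-up. The cost is one rewritten paragraph, with the same assessments, data and software.

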**Methods:**

In a randomized, controlled clinical trial, 105 postmenopausal women will be randomly assigned to three groups receiving vitamin D vaginal suppository, placebo vaginal suppository, or control (no intervention). Vitamin D vaginal suppositories contain 1000 units of vitamin D3. The timing of the use of vitamin D vaginal suppositories and placebo suppositories will be every night in the first 2 weeks, and every other night in the following 6 weeks (8 weeks in total). The primary outcome will be the sexual function of participants which will be assessed using the Female Sexual Function Index (FSFI) before and immediately after the intervention, and at 1 and 2 months after the end of the intervention. The side effects of these suppositories will be examined as a secondary consequence of the study. Data will be analyzed using SPSS software version 25. In the case of normal distribution of data, the mean score of sexual function will be compared between the groups using a repeated measurements ANOVA. If statistical analysis leads to significant results, the post-hoc test will be used to determine the differences between the groups. Comparison of demographic and fertility characteristics of the women will be carried out using statistical tests such as chi-squares and *t*-tests. A significance level of *p* < .05 will be used for statistical analyses.

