Problems with vaginal atrophy are clinically manifested 4–5 years after the beginning of menopause [8]. Vulvovaginal atrophy lead to vaginal dryness, irritation, soreness, and consequently dyspareunia [9, 10]. Approximately one-third of postmenopausal women report painful intercourse (dyspareunia), lack of moisture, and decreased lubrication [11]. Common symptoms of atrophy include vaginal dryness, burning, post-coital bleeding, and pain [12]. In clinical examination, symptoms such as being pale, the reduction of transverse vaginal folds (roga), petechiae, reduced elasticity, and dryness confirms the presence of atrophy [5]. Vaginal atrophy is one of the causes of sexual problems, and is one of the most important complaints among women during the menopause, but despite many advances in the prevention and treatment of menopausal complications, sexual problems are underestimated [13].

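### The demographic and fertility data are used only for baseline significance tests, which cannot inform the FSFI comparison; naming age, and years since menopause if recorded, as fixed covariates would be a cheap, modest gain in precision (minor)

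*Protocol article*

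**What the plan says.** The trial has three arms: "105 postmenopausal women will be randomly assigned to three groups", 35 per arm (Sample size estimation). The Randomization section describes simple randomisation and names no stratification factor.

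For baseline data, Data management and analysis says: "Comparison of demographic and fertility characteristics of the women in the groups will be performed using appropriate statistical tests". The sentence goes on to name the tests: "performed using appropriate statistical tests such as chi-square tests and one-way ANOVAs". The Abstract's Methods paragraph describes the same comparison differently: "Comparison of demographic and fertility characteristics of the women will be carried out using statistical tests such as chi-squares and *t*-tests". Neither place says what follows from a significant or non-significant result.

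For the primary outcome, "comparison of the mean scores of sexual function between the groups will be carried out using the repeated measurements ANOVA test". Transformation is the first response to non-normality, and then "If not, a mixed effect model or non-parametric statistics will be used". No covariate is named for any of these analyses.

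The document gives some reason to think that time since menopause matters. The Background says that atrophy problems are "clinically manifested 4–5 years after the beginning of menopause", and Goals and hypotheses expects the suppository to act on sexual function through atrophy. Eligible ages run from 45 to 65 years.

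**The concern.** Three things in the stated text sit badly together.

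First, in a properly randomised trial every baseline null hypothesis is true by construction. A significant baseline test is therefore a chance event, and a non-significant one does not show that the arms are alike.

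Second, the two places name different tests, and a t-test cannot compare three arms in one step.

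Third, testing is the only use the plan states for these data. With simple randomisation and about 35 women per arm, chance differences in age or years since menopause are to be expected. Covariates fixed in advance would remove the part of that noise that predicts FSFI. What is at stake is some interval width, and how a chance imbalance is handled once the data are seen. The validity of the comparison is not at stake.

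**Working it through.** The plan gives no figure of its own on this point, so there is none to reproduce. The inputs from the document are three arms, 35 per arm randomised, 25 per arm before the allowance for loss, a significance level of 0.05 and a planned effect size of 0.6. Equal arms are assumed throughout. Number of characteristics, correlations and imbalance sizes are also assumptions, because the document gives none of them.

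**What the baseline tests would show by chance**
- One ANOVA per characteristic, k independent characteristics: P(at least one p < .05) = 1 − 0.95^k. For k = 5, 8, 10 and 12 this is 23%, 34%, 40% and 46%.
- Three pairwise t-tests per characteristic at 35 per arm: simulation gives about 12% per characteristic, against 5% for one ANOVA. Over ten independent continuous characteristics this is 1 − 0.88^10 = 72%. The ten and the independence are illustrative; real characteristics are correlated and some are categorical.

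**What the tests would miss**
- Two-arm t-test at 35 per arm: the observed difference must exceed t(0.975; 68) × √(2/35) = 1.995 × 0.239 = 0.48 SD. At 25 per arm it is 0.57 SD.
- One-way ANOVA with the third arm midway: F = n·d²/4, so d must exceed √(4 × 3.085/35) = 0.59 SD.

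**How far a chance imbalance moves the unadjusted contrast**
- Shift = r × imbalance. For an imbalance of 0.4 SD and r = 0.3 to 0.5: 0.3 × 0.4 = 0.12 SD and 0.5 × 0.4 = 0.20 SD.
- How often: 0.4/√(2/35) = 0.4/0.239 = 1.67 standard errors, reached or exceeded in either direction in about 9% of randomisations for a given covariate and pair of arms.
- If the 0.6 is a standardised mean difference, which the document does not say, these shifts are 0.12/0.6 = 20% and 0.20/0.6 = 33% of it.

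**What adjustment buys**
- Interval width factor √(1 − r²), with r the (multiple) correlation of the covariate set with FSFI: r = 0.2 gives 0.980, 0.3 gives 0.954, 0.5 gives 0.866. Intervals are 2%, 5% and 13% narrower.

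**What adjustment costs**
- Error degrees of freedom for the between-group comparison: 3 × 35 − 3 = 102, or 3 × 25 − 3 = 72 with 25 completers per arm. Two covariates leave 100 or 70.
- Estimating two coefficients inflates the variance on average by 1 + 2/(ν − 3), for ν = 72 or 102: 1 + 2/69 = 1.029, or 1 + 2/99 = 1.020. In width this is about 1.4% or 1.0%.
- Net at 25 per arm: r = 0.2 gives 0.980 × 1.014 = 0.994; r = 0.5 gives 0.866 × 1.014 = 0.878. At the low end the gain nearly disappears; at the high end about 12% remains.

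**The case against.** The strongest objection is that the covariate half rests on silence. The text neither lists covariates nor excludes them, and a condensed article commonly leaves such a list to a full protocol or SAP that is not shown. That stands against saying that the plan ignores age and years since menopause. It does not remove what the text does state: baseline tests with no use, two different test lists, and an FSFI analysis described without covariates.

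A reader might also infer that the arms' comparability will be judged by these p-values. The text says only that characteristics will be compared. It gives no balance rule and no step from a test result to the analysis, so that reading is not supported.

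A reader might further infer that the treatment estimate is biased. It is not. Chance imbalance under randomisation is already reflected in the standard error of the unadjusted comparison. The 0.4 SD example is a selected, fairly uncommon case. FSFI is measured before and after treatment, so if the repeated-measures analysis treats baseline as a time point, any effect of age or years since menopause that is constant over time cancels from the group-by-time contrast. The shift and the precision gain then both shrink.

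Three lesser objections also stand. Both test lists are introduced as examples, and the Methods already name a suitable three-arm test, so the mismatch is small. The Background statement concerns when atrophy appears, not FSFI scores, so the prognostic case is indirect. Years since menopause is not listed as a variable to be collected; only age is certain to be known, because it is an eligibility criterion.

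**Conclusion.** The point holds as a minor one. The planned baseline tests cannot inform the FSFI comparison, and the two descriptions of them differ. Removing the p-values or reconciling the test names would change no result. The change with some statistical value is to use age, and years since menopause if available, as covariates fixed in advance. That is a better use of the data than testing them, and it also leaves no room to choose covariates after seeing the balance.

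The benefit is about 2% to 13% in interval width for assumed correlations of 0.2 to 0.5, before the 1.0% to 1.4% average cost of estimating two coefficients, and smaller again once baseline FSFI is in the model. If the covariates are unrelated to FSFI there is no gain, only that small cost. The unadjusted comparison remains valid throughout.

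**What to change.** In Data management and analysis, state that the FSFI model (repeated-measures or mixed) includes age, and years since menopause if it is recorded at screening, as fixed covariates whatever their observed balance, with the unadjusted result reported as a sensitivity analysis. If a fuller document already lists covariates, align the article with it.

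In the same section and in the Abstract's Methods paragraph, replace the tests of baseline characteristics with summaries by arm without p-values. This also removes the t-test/ANOVA mismatch.

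The cost is a few sentences, no extra participants, and about two degrees of freedom out of roughly 72 (25 completers per arm) or 102 (35 per arm). If years since menopause is not already asked, it adds one screening question.
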